#### Modifications

The specific stopping criteria are as follows: (1) adverse reactions or serious complications occurring in patients during clinical treatment; (2) significant errors in the established clinical trial protocols, making it difficult to evaluate the efficacy of the treatment; and (3) significant deviations in the implementation of a well-designed protocol, making it difficult to evaluate the therapeutic effect.

#### Confidentiality

Each participant’s privacy will be maintained to the extent permitted by law. Ombudsmen, inspectors, ethics committees, and regulatory authorities will be granted direct access to participants’ original medical records to verify clinical trial procedures and data to the extent permitted by applicable laws and regulations and without infringing on participants’ privacy. The personal data of the participants will be kept confidential.

#### Amendments

All amendments and adjustments to this protocol must be agreed upon and signed by all study investigators. The amendments will be submitted to the Ethics Committee for approval and updated in the clinical trial registry.

### Statistical Methods

#### Primary and Secondary Outcomes

Continuous variable data following a normal distribution will be expressed using means (SDs), while those not following a normal distribution will be expressed using medians and quartiles. Categorical data will be depicted as component ratios or percentages. Group comparisons for continuous variables will be conducted using independent samples *t* tests and repeated-measures ANOVA (multiple time-point comparisons). Nonparametric data comparisons will be carried out using rank-sum tests. Categorical variables will be compared using chi-square tests or Fisher exact tests. All data analyses and graph representations will be processed using R 4.0.l software (R Project for Statistical Computing). Statistical significance will be defined as *P*<.05.

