### Eligibility Criteria

#### Inclusion Criteria

The inclusion criteria are as follows: (1) age between 18 and 60 years, regardless of sex; (2) meeting the diagnostic criteria for CSU; (3) wheals and itching occurring continuously for at least 6 weeks before enrollment (despite using H1 antihistamines; occurring at least once daily) and wheals and itching being the main symptoms (without severe systemic symptoms); (4) a UAS7 of ≥16 and a weekly pruritus score of ≥8; (5) no history of ACE; and (6) signing of informed consent and volunteering to participate in the study.

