### Sample Size

Referring to relevant literature [17], a formula for the superiority test is used to calculate the sample size:

where *c*=1, *n*_2_=*n*_1_; if α=.05, *u*_1_-*T*=1.64 and *u*_1_-*u*=1.28.

According to previous research [15] based on the UAS7 as the main therapeutic evaluation index, *e* is set at 9.12, *W* is set at 6, and the data are substituted into the formula to calculate *n*_1_=*n*_2_≈40. Considering a 25% dropout rate, we establish a sample size of 54 cases in each group, with a total of 108 cases.

However, it is worth noting that when conducting MRI research on the human body, the calculation of sample size does not strictly adhere to the methods used in clinical trials. Currently, there are no clear guidelines for determining sample size in fMRI studies. After an extensive review of the literature spanning the past decade, we did not find a standardized sample size calculation method for experimental studies involving brain fMRI. The previous results of the research group showed that 20 cases in each group met the statistical and practical requirements [13,14]. In this study, 40 subjects are selected for fMRI examination based on the results of previous studies and the scale of the subjects.

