### Outcomes

The study schedule is presented in Figure 3. All outcome measures explained below will be recorded from baseline until the end of follow-up.

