#### Primary Outcome

The primary outcome measure for this clinical trial will be the UAS7. The UAS7 is the gold standard for CSU, evaluating 2 skin symptoms: wheals and itching. Participants will self-assess and record the severity of their symptoms on a 4-point scale. For itchiness, the scoring will be as follows: 0, no symptoms; 1, mild symptoms (occasional itching, no scratching, and no effect on life and sleep); 2, moderate symptoms (occasional itching, scratching, and life and sleep slightly disturbed, but tolerable); 3, severe symptoms (frequent itching, scratching, life and sleep disturbed, and intolerable). For wheals, the scoring will be as follows: 0, no symptoms; 1, mild symptoms (<20 in 24 h); 2, moderate symptoms (21-50 in 24 h); 3, severe symptoms (>50 in 24 h or large confluent masses). The UAS7 ranges from 0 to 42, with lower scores indicating milder skin symptoms [23].

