## Results

Recruitment began on March 1, 2023. A total of 4-6 participants are expected to be enrolled per month. The recruitment is planned to be completed on March 1, 2025, and we expect to publish our results by the winter of 2025. As of November 1, 2023, we have enrolled 25 participants with CSU.

To compare all the results, including both primary and secondary outcomes, and evaluate the treatment effect, we will use R (version 4.0.1) for the analyses. ANOVA and independent samples *t* tests will be repeatedly performed for determining differences in variables between baseline and posttest in the treatment and control groups and for comparing the effects of the program between the groups. Moreover, we will determine whether there is a significant difference between the groups by judging the rejection range based on a significance level of .05. Drawing upon the outcomes of prior research, we anticipate that when comparing the primary and secondary efficacy indicators across the intervention and baseline periods, both the treatment and control groups will exhibit a downward trend in scores. However, it is expected that the decrease will be more pronounced and significant in the treatment group.

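### The between-group tests fixed for UAS7 make no covariate adjustment for baseline UAS7, which every participant has; they are valid but give up precision at no saving

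*Protocol article*

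**What the plan says.** The primary outcome is fixed in Primary Outcome: "The primary outcome measure for this clinical trial will be the UAS7".

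Statistical Methods (Primary and Secondary Outcomes) gives the analysis: "Group comparisons for continuous variables will be conducted using independent samples *t* tests and repeated-measures ANOVA (multiple time-point comparisons". Rank-sum tests are the fallback for nonparametric data. The Results section describes it again: "ANOVA and independent samples *t* tests will be repeatedly performed for determining differences in variables between baseline and posttest in the treatment and control groups", followed by a comparison between groups. The Abstract also names ANOVA and t tests. No section mentions ANCOVA, a mixed model or any covariate.

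The baseline value is available for everyone. Inclusion Criteria requires "a UAS7 of ≥16 and a weekly pruritus score of ≥8", and Outcomes states: "All outcome measures explained below will be recorded from baseline until the end of follow-up".

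**The concern.** In a randomized trial with a continuous score measured before and after treatment, the baseline score is usually the best single predictor of the follow-up score. Using it as a covariate removes the part of the outcome variance that it explains and corrects the estimate for chance imbalance at baseline. The stated tests do neither in that form. A t test on follow-up scores does not use baseline at all. A change-score test, or a group-by-time contrast, subtracts baseline with a fixed weight of one, which is generally not the best weight.

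At stake is power in a trial whose authors list small sample size as a limitation and plan for 25% dropout. There is a second, conditional risk. If baseline is entered as one of the repeated time points and the group main effect is read as the treatment test, the effect is averaged with a visit at which randomization makes the expected difference zero.

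**Working it through.** **Inputs.** From Sample Size: "if α=.05, *u*_1_-*T*=1.64 and *u*_1_-*u*=1.28"; *e* = 9.12 and *W* = 6; "the data are substituted into the formula to calculate *n*_1_=*n*_2_≈40"; 25% dropout, 54 per arm. The formula itself is not legible in the text, so I read 9.12 as the SD and 6 as the difference. Assumed, because the article does not give it: baseline/outcome correlation ρ of 0.3, 0.5 or 0.7, with 0.2 as a low case. I also assume equal SDs at baseline and follow-up.

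**1. Reproduce the plan's figure.** n = 2[(1.64 + 1.28) × 9.12 / 6]² = 39.4, so 40 per arm. The opposite reading (SD 6, difference 9.12) gives 7.4, so the reading used here is the one that fits. Then 40 / 0.75 = 53.3, so 54 per arm and 108 in total. The stated size reproduces as a one-sided .05, 90% power, unadjusted comparison of two means.

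**2. Unadjusted power with 40 per arm.** The noncentrality parameter is 6 / [9.12 × √(2/40)] = 2.94, with 78 degrees of freedom. Power by the noncentral t is 89.8% one-sided and 82.8% two-sided. Statistical Methods sets P<.05 without stating sidedness.

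**3. ANCOVA power.** The residual SD depends on what 9.12 is:
- follow-up SD: 9.12 × √(1 − ρ²)
- change-score SD: 9.12 × √((1 + ρ)/2), since the ANCOVA variance σ²(1 − ρ²) divided by the change variance 2σ²(1 − ρ) is (1 + ρ)/2

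| ρ | Variance cut, follow-up SD | Two-sided power | Variance cut, change SD | Two-sided power |
|---|---|---|---|---|
| 0.3 | 9% | 86% | 35% | 95% |
| 0.5 | 25% | 92% | 25% | 92% |
| 0.7 | 51% | 98% | 15% | 88% |

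The unadjusted comparator is 83% in every row: a follow-up-score t test under the first reading, a change-score t test under the second. At ρ = 0.2 with a follow-up SD, power is 84%. On the one-sided basis of the sample size, power rises from about 90% to 92%, 96% and 99% (follow-up SD) or 98%, 96% and 94% (change SD). The extra covariate costs one degree of freedom, which changes none of these figures.

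**4. Change score instead of ANCOVA.** If 9.12 is the follow-up SD, the change-score SD is 9.12 × √(2(1 − ρ)). At ρ = 0.3 that is 10.8, and two-sided power is 69%, below the 83% obtained by ignoring baseline. At ρ = 0.5 the two are equal. Above 0.5 the change score does better than the follow-up score but not better than ANCOVA (at 0.7, 96% against 98%).

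**5. Baseline as a time point, main effect read.** With k post-baseline visits, a constant effect and equal correlations, the effect becomes 6k/(k + 1) and the SD 9.12 × √((1 + kρ)/(k + 1)). For k = 1, two-sided power is 44%, 39% and 35% at ρ = 0.3, 0.5 and 0.7. For k = 4 it is 94%, 85% and 76%. Averaging the same four visits without baseline (effect 6, SD 9.12 × √((1 + 3ρ)/4)) gives 99%, 96% and 91%. Dilution therefore occurs in both cases, but its size depends heavily on the number of visits.

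**The case against.** The strongest reply is that the stated tests are conventional and valid, that the trial meets its own sizing basis, and that a condensed article need not carry every modelling detail. The first two parts stand: an unadjusted randomized comparison is unbiased, and on one-sided terms the design has about 90% power. The third does not remove the point, because the article specifies the tests itself.

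A reader might infer several stronger claims that the documents do not support:

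- **That the repeated-measures ANOVA has power of only about 35% to 44%.** This requires both that the group main effect is the test and that there is a single post-baseline visit. Neither is stated. The method is said to be for multiple time points, and the Results wording fits a change or group-by-time comparison at least as well. The schedule figure is not available in the text. With four post-baseline visits, the main effect at ρ = 0.3 or 0.5 has more power than the single-visit t test.
- **That true power is 83% because baseline is unused.** The drop from 90% to 83% comes from moving from a one-sided to a two-sided test, not from the lack of adjustment.
- **That needing complete profiles breaks the sample size.** The increase from 40 to 54 per arm already allows for 25% dropout, and handling of individual missed visits is normally left to the analysis plan.
- **That baseline goes wholly unused.** Under the change-based reading of Results it is used, though not in the most efficient way.

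The size of the gain is also uncertain. The correlation is unknown, the UAS7 entry threshold may lower it, and the direction in which the gain varies with ρ reverses with the type of SD.

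**Conclusion.** The point holds as one of efficiency. It does not show bias or an invalid test. The article fixes unadjusted between-group tests for its primary outcome while holding the baseline value on every participant. With 40 evaluable per arm, baseline adjustment raises two-sided power from 83% to between 86% and 98% if 9.12 is a follow-up SD, or to between 88% and 95% if it is a change-score SD, over assumed correlations of 0.3 to 0.7. The gain is about one percentage point at a correlation of 0.2 under the follow-up reading. ANCOVA shows no loss in any case examined. Main-effect dilution is a risk only if baseline is a time point and that term is the test, and it cannot be sized without the visit schedule. The change is worth making, but the trial remains interpretable without it.

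**What to change.** Replace the t test and repeated-measures ANOVA as the primary between-group analysis with one of the following:

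- an ANCOVA of UAS7 at one prespecified time point (for example, the end of the 8-week treatment), with treatment as factor and baseline UAS7 as covariate; or
- a likelihood-based mixed model over all post-baseline visits with baseline UAS7, visit, treatment and treatment-by-visit, from which the contrast at that time point is reported.

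Report the contrast with a 95% CI. Keep baseline out of the outcome vector. Analyse the secondary scales the same way, each with its own baseline as covariate.

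The cost is analysis wording only: no extra data, visits or participants. The change should go through the route in Amendments (investigators' agreement, ethics committee, registry update) and be in place before the unblinding planned for the end of case collection.

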### Randomization, Concealment, and Blinding

Random numbers will be generated using the Statistical Analysis System PROC PLAN process statement to determine the number of seeds and the segment length. Treatment assignments corresponding to running numbers 001-108 will be listed. To ensure allocation concealment, the randomization process will be managed by an independent statistician who is not involved in the study. Eligible participants will be randomly assigned to the treatment or control group in a 1:1 ratio.

Random numbers will be sealed in an opaque envelope, which will be stored in the study center. To ensure the objectivity of the research, operators and efficacy evaluators will be strictly distinguished, and efficacy evaluators and statisticians will be blinded. Only operators will have access to random numbers before treatment, and they will not be involved in the evaluation process. The selected acupoints are mainly on the lower limbs and back. The control group will also undergo acupuncture, which will ensure patient blinding. Two-stage unblinding will occur only at the end of the case collection.

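### UAS7 is compared between groups without baseline UAS7 as a covariate: the planned test is valid, but it is no more precise than ANCOVA and leaves chance baseline imbalance in the estimate

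*Protocol article*

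**What the plan says.** Statistical Methods (Primary and Secondary Outcomes) fixes the between-group method: "Group comparisons for continuous variables will be conducted using independent samples" t tests, with repeated-measures ANOVA for several time points and rank-sum tests for nonparametric data. The Abstract names ANOVA and t tests as well. The Results section applies them to baseline-to-posttest differences within the groups "and for comparing the effects of the program between the groups". No section names ANCOVA, a baseline covariate or any other adjustment.

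The baseline value exists for everyone. Entry requires "a UAS7 of ≥16 and a weekly pruritus score of ≥8", and the Outcomes section says that all measures "will be recorded from baseline until the end of follow-up". Allocation is simply 1:1 ("Eligible participants will be randomly assigned to the treatment or control group in a 1:1 ratio"), and no stratification by baseline UAS7 is mentioned.

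**The concern.** The wording allows two main readings, and neither uses baseline UAS7 as well as it could be used.

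- A t test on the post-treatment score ignores baseline.
- A t test on change, or the group-by-time test with baseline as one of two time levels, uses baseline with a fixed coefficient of 1 instead of the slope that the data support.

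ANCOVA estimates that slope. Its residual variance is never larger than that of either alternative, apart from one degree of freedom.

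Two things are at stake. The first is power in a trial that plans on about 40 evaluable patients per arm and lists its small sample among its limitations. The second is the estimate itself: with no stratification on baseline severity, a chance difference between the arms at baseline shifts the post-score and change-score contrasts, usually in opposite directions. The article does not say which contrast decides.

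**Working it through.** **Inputs from the article (Sample Size).** The two numerical planning values are 9.12 and 6, read here as SD and difference. The quantiles are "if α=.05, *u*_1_-*T*=1.64 and *u*_1_-*u*=1.28". Dropout and total: "Considering a 25% dropout rate, we establish a sample size of 54 cases in each group, with a total of 108 cases".

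**Reproducing the plan's figure.** n per arm = 2 × (1.64 + 1.28)² × 9.12² / 6² = 39.4, so 40; and 40 / 0.75 = 53.3, so 54. Both match. Swapping the roles of 6 and 9.12 gives n = 8, which confirms the reading. The stated size is therefore that of an unadjusted, one-sided two-sample comparison with 90% power, and it contains no baseline correlation.

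**Assumptions not in the article.** These are the baseline-outcome correlation r (0.3, 0.5, 0.6), 9.12 as the SD of the post-treatment score (s1), and the baseline SD (s0), taken either as 9.12 or as 6. The value 6 only illustrates a baseline range narrowed by the entry threshold. Tests are two-sided at .05, since the analysis section gives no side.

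**Formulas.**
- Post-score SD: s1 = 9.12.
- Change-score SD: √(s0² + s1² − 2·r·s0·s1).
- ANCOVA residual SD: s1·√(1 − r²).
- Power from the noncentral t with 40 per arm; ANCOVA is charged one degree of freedom (77 instead of 78).

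**Power for a 6-point difference.**

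| Analysis | r = 0.3 | r = 0.5 | r = 0.6 |
|---|---|---|---|
| Post-score t test | 82.8% | 82.8% | 82.8% |
| Change score, s0 = 9.12 | 69.0% | 82.8% | 90.1% |
| Change score, s0 = 6 | 81.4% | 91.0% | 95.2% |
| ANCOVA | 86.1% | 91.8% | 95.3% |

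Gain of ANCOVA over the post-score test: about 3, 9 and 12.5 points. Over the change score with s0 = 9.12: about 17, 9 and 5 points. Over the change score with s0 = 6: 4.7, 0.8 and 0.1 points.

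**If 9.12 is the SD of change instead** (equal SDs at both times, normal approximation): the ANCOVA SD is 9.12·√((1 + r)/2), and power rises from 83.7% to 95.4%, 92.5% and 89.1% at r = 0.3, 0.5 and 0.7.

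**Chance imbalance.** The SE of the baseline difference is s0·√(2/40).
- s0 = 6: SE 1.34, so 1.96 × SE = 2.6 points.
- s0 = 9.12: SE 2.04, so 1.96 × SE = 4.0 points.

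A baseline difference d shifts the post-score contrast by slope × d and the change-score contrast by (slope − 1) × d, where slope = r·s1/s0. With s0 = 6 the slope is 0.456 at r = 0.3 and 0.76 at r = 0.5. A 2.6-point imbalance then moves the post-score contrast by 1.2 to 2.0 points and the change-score contrast by −1.4 to −0.6 points. ANCOVA removes the part explained by the linear slope.

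**The case against.** The strongest reply is that this is a matter of efficiency, not an error. Under 1:1 randomisation the planned comparison is unbiased on average and controls type I error, and it matches the formula used to size the trial. That stands. It does not make the point moot, because the article names the method in three places. An analysis plan consistent with it would run these tests.

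A second reply is that the Results section speaks of baseline-to-posttest differences and expects a larger decrease under treatment. This fits a change score or a group-by-time test at least as well as a post-score test, so baseline may not be ignored. That also stands. It is why the change-score rows belong beside the post-score row, and why the gain can be under 1 point.

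Third, the entry threshold may lower r, which pushes the gain over a post-score test towards the low end. On the one-sided scale of the sample size calculation, power at r = 0.3 moves only from 89.8% to 92.1%. This limits the size of the gain, not its direction.

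Two stronger readings are tempting and not supported:

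- A reader might infer that the ANOVA would be badly underpowered because its group main effect averages in the baseline visit. With baseline plus a single post visit (r = 0.5, baseline SD 6) that test has about 52% power. But the article plans several time points, and with the same inputs and a constant effect the figure is 76% to 90% with two to four post visits. The stated hypothesis of a greater decrease also corresponds to the interaction, not the main effect.
- A reader might infer that a baseline difference carries over in full to the post-treatment comparison. It does so only in proportion to the slope, as shown above.

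**Conclusion.** The point holds as one of precision and conditional imbalance. The stated between-group analysis never uses baseline UAS7 as a covariate, although every participant supplies it. No reading of the plan as a post-score or change-score test is more precise than ANCOVA, apart from one degree of freedom.

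On the article's planning values the gain ranges from negligible (change score, baseline SD 6, r = 0.6) to about 17 percentage points of power (change score, baseline SD 9.12, r = 0.3). Where in that range the trial lies depends on r, on the baseline SD and on which contrast is tested; the article gives none of the three. The conclusion does not extend to invalidity, bias on average, or a wrong sample size for the unadjusted one-sided test. The change is worth making because it is cheap and cannot do material harm to precision.

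**What to change.** In Statistical Methods, and to match in the Abstract and Results, make the between-group analysis of UAS7 an ANCOVA at the primary time point, with treatment group and baseline UAS7 as terms. A repeated-measures model of the post-baseline visits would serve equally, with baseline as a covariate and not as a time level. Report the adjusted mean difference with its 95% CI. The primary time point has to be named for this to work, because the statistical section does not name one. Analyse CU-Q2oL, DLQI, UCT, SAS, SDS and ISI the same way, each with its own baseline. State how the rank-sum route for non-normal data relates to this analysis, for example as a sensitivity analysis, so that baseline is not dropped whenever that route is taken.

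Cost: one degree of freedom, with no new data and no extra patients. Recruitment has begun (25 enrolled by November 1, 2023), so the change needs the process in the Amendments section: sign-off by all investigators, ethics approval and a registry update. It should be completed before unblinding.
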